##### Implementation intervention strategies

Table 1 lists the implementation strategies that will be used to support the introduction of the model of care for addressing maternal alcohol consumption during pregnancy (Fig. 2), including the evidence source and the TDF domains on which each strategy was based and the barriers that the strategy was intended to address.

**Table 1 Tab1:** Implementation intervention strategies

Implementation strategy	TDF domain/s [56]	Identified barriers strategy seeks to overcome	Mapped behaviour change techniques [43]	Strategy description
1. Leadership/managerial supervision [65]	• Professional role • Belief about consequences	• Clinician belief that it is not their responsibility to routinely address alcohol consumption during pregnancy. • Clinician and manager belief that there are more important things to do. • Manager belief that they lack support from colleagues to manage staff performance and that staff are resistant to clinical practice change. • Clinician belief that they will not be held accountable if they do not address alcohol consumption. • Clinician belief that their managers do not expect alcohol care to be delivered.	• Social processes of encouragement, pressure and support • Persuasive communication	• Throughout planning and implementation, monthly meetings will be held with management from antenatal services within each of the participating sectors to gather feedback on planned strategies and elicit support. • Antenatal service managers will be asked to distribute key documents/communications to staff and attended all training sessions. • Antenatal service managers will have performance measures related to the model of care added to their operational plans.
2. Local clinical practice guidelines [66]	• Knowledge • Environmental context and resources	• Clinician lack of knowledge of the procedure for addressing alcohol consumption, including referral pathways for women requiring further support. • Clinician feedback that IT systems/forms do not support required care. • Clinician belief that they do not have a clear plan for addressing alcohol consumption during pregnancy and if they have a problem they do not know how to solve it.	• Information regarding behaviour/outcome • Environmental changes • Goal target specified: behaviour or outcome • Contract • Planning and implementation	• A service level guideline and procedure document will detail the required care for addressing alcohol consumption during pregnancy, including assessment, brief advice and referral pathways. • The guidelines and procedure will be uploaded onto the health service’s policy, procedure and guidelines directory and disseminated by service managers to all staff via email and hard copies will be placed in staff common areas.
3. Electronic prompt and reminder system [67]	• Memory, attention and decision processes • Environmental context and resources • Behavioural regulation	• Clinician feedback that they often forget to address alcohol consumption during pregnancy and do not unless the woman expresses it as a priority. • Clinician feedback that IT systems/forms do not support required care. • Clinician feedback that there is a lot to cover in antenatal appointments. • Clinician belief that they do not have a clear plan for addressing alcohol consumption during pregnancy and if they have a problem they do not know how to solve it.	• Environmental changes • Prompts, triggers and cues	• Modifications will be made to existing point-of-care and medical record systems used by maternity clinicians to electronically prompt standardised assessment of alcohol consumption using the validated AUDIT-C alcohol screening tool. Brief advice scripts will be displayed on the point-of-care system based on the woman’s AUDIT-C risk score, as will prompts and tools for referral to appropriate services.
4. Local opinion leaders/ champions [65, 68, 69]	• Social/professional role and identity • Motivation and goals • Social influences	• Clinician belief that it is not their responsibility to routinely address alcohol consumption during pregnancy. • Clinician and manager belief that there are more important things to do. • Clinician belief that other staff do not routinely undertake the model of care and there is no one who can provide support if a problem is encountered. • Manager belief that they lack support from colleagues to manage staff performance and that staff are resistant to clinical practice change.	• Social processes of encouragement, pressure, support • Persuasive communication • Modelling, demonstration of behaviour by others	• Project-specific Clinical Midwife Educators (CMEs) will be appointed to support staff to uptake the model of care and will provide support at a one-on-one, team and service level. The CMEs will be appointed based on their ability to engage and influence staff and model-required behaviours. The role of the CME will be to deliver and monitor each of the implementation support strategies and be responsive to the specific implementation needs of each antenatal service. • Additional local antenatal clinical leaders will be engaged to provide encouragement and demonstration of required behaviours in each antenatal services as required (e.g. for specific professional disciplines).
5. Educational meetings and educational materials [70, 71]	• Knowledge • Skills • Beliefs about capabilities • Beliefs about consequence • Environmental context and resources • Emotion	• Clinician lack of knowledge in the procedure for addressing alcohol consumption, including referral pathways for women requiring further support. • Clinician lack of skill in assessing alcohol consumption during pregnancy using a validated tool and offering referrals to women requiring further support. • Clinician lack of training in addressing alcohol consumption according to guidelines. • Clinician belief that they have limited capability to assess alcohol consumption during pregnancy using a validated tool and offer appropriate referrals. • Manager belief that they have limited capability to competently use performance monitoring tools and reports and have conversations with staff regarding performance. • Clinician belief that pregnant women will react negatively if asked about alcohol consumption and that it will have a negative impact on their client-clinician relationship. • Clinician feedback that they are hesitant to address alcohol due to child protection implications. • Clinician belief that they do not have access to appropriate information resources and there is a lack of support services to refer women to. • Clinician lack of confidence in addressing alcohol consumption in appointment time, when other clinicians are present and when women show lack of interest. • Clinician feedback that they feel nervous and uncomfortable addressing alcohol consumption with women.	• Goal/target specified behaviour or outcome • Increasing skills- through problem solving, decision-making, goal-setting • Rehearsal of relevant skills • Modelling/ demonstration of behaviour by others • Perform behaviour in different settings • Social process of encouragement/ pressure support • Persuasive communication • Information regarding behaviour/ outcome • Coping skills	• Training will be provided to all antenatal service clinicians via a 30-minute online training module and face-to-face sessions. Content will be adapted from the accredited ‘Women Want to Know’ courses [72]. The CME will facilitate clinicians completing the online training and coordinate face-to-face training sessions, which will be rostered into routine clinical meetings and include, lecture style sessions, interactive, case-study based sessions and one-on-one sessions. • Training content will include: − The effects of alcohol consumption during pregnancy and associated health outcomes. − Guideline recommendations for alcohol consumption during pregnancy. − Prevalence of alcohol consumption by pregnant women. − The model of care for addressing alcohol consumption during pregnancy: 1) alcohol consumption assessment; 2) brief advice; and 3) referral for ongoing care. − Effectiveness and acceptability of addressing alcohol consumption during pregnancy in routine antenatal care. − Culturally appropriate practices when addressing alcohol consumption with Aboriginal women. • Clinicians will also be provided with written resources (hardcopy and electronic) to support the model of care, including standard drink measure charts and point-of-care written prompts/reminders (e.g. stickers in charts).
6. Academic detailing, including audit and feedback [45, 73, 74]	• Behavioural Regulation • Skills • Beliefs about consequences • Social Influences	• Clinician belief that they do not have a clear plan for addressing alcohol consumption during pregnancy and if they have a problem they do not know how to solve it. • Clinician lack of skill in addressing alcohol consumption according to guidelines. • Manager belief that additional burden will be placed on clinicians, that staff will react negatively if performance is discussed and that staff will not take on board feedback about performance. • Manager feedback that it is difficult to release clinicians from clinical work to attend training. • Clinician belief that pregnant women do not expect alcohol to be addressed in antenatal appointments.	• Goal/target specified behaviour or outcome • Monitoring • Contract • Planning, implementation • Increasing skills- problem solving, decision-making, goal-setting • Rehearsal of relevant skills • Social process of encouragement/pressure support • Feedback • Persuasive communication • Information regarding behaviour and outcome	• Data from both medical records and telephone surveys conducted with women who attended the antenatal services will be used to provide feedback on levels of care provision for addressing alcohol consumption during pregnancy. • Data will routinely be fed back to antenatal service teams by the CME. The CME will visit service teams in their antenatal clinics to support discussion of the feedback and development of action plans in response to such in order to improve care. • Women’s acceptability of their antenatal service team providing each of the care elements will also be fed back.
7. Monitoring and accountability for the performance of the delivery of healthcare [73]	• Social Influences • Beliefs about capabilities • Environmental context and resources • Memory, attention, decision processes	• Clinician belief that their managers do not expect alcohol care to be delivered. • Manager belief that they have limited capability to competently use performance monitoring tools and reports and have conversations with staff regarding performance. • Manager feedback that they do not have adequate data entered from staff to use for performance measurement, have competing work tasks and do not have the supports/resources to manage performance. • Managers’ feedback that they forget about tools to manage performance and are less likely to manage performance of staff resistant to change. • Manager feedback that it is stressful to manage performance.	• Social processes of encouragement, pressure, support • Environmental changes • Contract • Prompts, triggers, cues • Feedback	• Antenatal service managers will be supported by the CME to report, interpret and monitor performance measures for the model of care for addressing alcohol consumption during pregnancy. The CME will also support these mangers to disseminate these results to their antenatal service staff through team meetings, emails and other usual communication mechanisms. • Performance measures will be built into the existing monitoring and accountability frameworks for antenatal services, including service-level operational plans and performance measures at service manager and team manager level.

##### Implementation intervention delivery timeline

The intervention strategies listed above will be implemented in each sector for 7 months prior to follow up data collection (Fig. 1). This will include a 1-month period introducing the practice change and a 6-month intensive practice change intervention. Given their organisational and system focus, all strategies, other than the local opinion leader (Clinical Midwife Educator (CME)) and academic detailing strategies, have the potential to continue to be implemented following the 7-month study intervention period, subject to the operational decisions of the Local Health District.

### Control and contamination

#### Usual care

Prior to implementation of the practice change intervention in each of the three sectors, usual antenatal care for addressing maternal alcohol consumption during pregnancy will be provided. Such care is likely to vary by antenatal service and clinician as no existing health sector-wide guideline or procedure specifies the provision of routine care for addressing alcohol consumption during pregnancy.

#### Potential for contamination

As the research team will control the initiation and delivery of all the intervention elements, the intervention strategies will not be accessible to antenatal clinicians during the baseline (control) phase. Although potential for contamination during this phase from staff movement between sectors is possible, it is considered to be limited due to the structural and systemic nature of the implementation strategies. Information on movement of clinicians between participating sectors will be collected throughout the study.

### Measures

#### Primary trial outcomes

There are four primary outcomes for this trial. They are the proportion of all antenatal clinic appointments (at ‘booking in’, 27-28 weeks gestation and 35–36 weeks gestation) for which women report:Being assessed for alcohol consumption and level of risk using the AUDIT-C.Being provided with brief advice related to alcohol consumption during pregnancy.Receiving, relative to their level of risk, the relevant elements of antenatal care for addressing alcohol consumption during pregnancy (advise and refer).Being assessed for alcohol consumption and level of risk using the AUDIT-C and receiving, relative to their level of risk, the relevant elements of antenatal care for addressing alcohol consumption during pregnancy (advise and refer).

#### Secondary trial outcome

For women attending antenatal appointments at ‘booking in’, 27–28 weeks gestation and 35–36 weeks gestation, alcohol consumption since pregnancy recognition as measured by total AUDIT-C score will be collected based on self-report of women. AUDIT-C is a validated tool for assessing risk of harm due to alcohol consumption [53].

#### Process evaluation measures

The acceptability, appropriateness, feasibility, intervention fidelity and reach of the model of care for addressing maternal alcohol consumption in pregnancy and the implementation strategies will be assessed via surveys of women and clinicians and project records. These process measures will be based on an implementation evaluation framework [61] and use validated measures where available [62]. Measures to assess implementation intervention reach will include participation of antenatal clinical staff in educational meetings, interaction with local opinion leaders, involvement in academic detailing/ audit and feedback sessions, and receipts of clinical practice guidelines. To determine reach of the implementation intervention strategies across different groups of clinicians, data will be collected from clinicians on position/profession, level of training, and length of time working in current antenatal service and in antenatal services generally. To assess delivery of the model of care across different demographic groups of women, the following information will be collected from pregnant women: age, gender, highest level of education, employment status, geographical location, Aboriginal or Torres Strait Islander status of woman and baby, household composition, current gestation, gestation at first antenatal clinic visit, whether attending care for first or subsequent pregnancy and alcohol consumption prior pregnancy (via AUDIT-C).

#### Cost and cost-effectiveness

To provide a measure of the investment required to develop, implement and maintain the effect of the implementation strategies, resource use will be prospectively measured and valued from a public finance perspective. The outcomes from the cost analysis will be (i) an estimate of the cost required to develop the intervention strategies, (ii) the net cost of delivering the implementation intervention (including labour costs for the CME and the clinicians to conduct/participate in each of the implementation strategies, undertaking quality assurance processes, providing managerial oversight), and (iii) assuming a positive trial outcome, the expected incremental cost to maintain effect. Additionally, the cost-effectiveness of the implementation strategies will be assessed relative to the baseline (current practice) phase in each of the three sectors. The incremental cost-effectiveness ratio (ICER) will be calculated as the difference in average cost between the intervention and baseline phases, divided by the difference in the primary outcome. Sensitivity analyses will test the robustness of results to selected issues and assumptions.

### Data collection procedures

#### Primary and secondary outcome measures

Each week a sample of women who in the past week attended an antenatal clinic for a ‘booking in’ visit, a visit when they were 27–28 weeks gestation, or a visit when they were 35–36 weeks gestation will be sent a letter providing information about the study and inviting them to participate in a computer assisted telephone interview (CATI) survey. Telephone contact will be attempted with women up to ten times over a 2-week period, including at different times of the day and on weekdays and weekends, in order to elicit consent and completion of the survey. If a woman declines to participate in the CATI, they will be invited to complete the survey online. If they consent to participate in the online survey, they will be sent a survey link via text message. Women who are of Aboriginal or Torres Strait Islander origin and/or are attending or enrolled to attend an AMIHS will be offered via text message the choice of participating in the survey via either CATI or online mode.

The CATI survey will be conducted by experienced female interviewers who will receive specific training and undertake practice interviews. The CATI and online survey script are identical in the wording of questions, response options and help provided. Both surveys will be pilot tested prior to starting the study to test comprehension, logic flow and survey length.

#### Process evaluation

Data for the aforementioned process evaluation measures will be collected via surveys with women (as per procedure described above) and clinicians. Online surveys of clinicians will be conducted at the completion of the intervention in each sector. All eligible clinicians in antenatal services in the participating sectors will be sent a link to an online survey via email, and also given the option to complete the survey on tablet computers/laptops in regular in-services and clinic meetings. Surveys will be completed anonymously. Additional process data to assess intervention fidelity and reach will be collected using project management logs completed by project staff.

#### Cost and cost effectiveness

Project management logs, including a cost capture template, will be used to prospectively collect data regarding the resources expended during intervention development and implementation.

#### Overall data management

Management of trial data will be in accordance with a data management protocol, which has been developed and approved by the project’s advisory group. Data will be stored securely as per the requirements of the Hunter New England Human Research Ethics Committee, The University of Newcastle Human Research Ethics Committee and the Aboriginal Health and Medical Research Council. Data will only be accessible to primary researchers and statisticians. Confidential participant data will be stored securely and not linked to survey responses.

### Sample size and power calculations

It is expected that 70% of invited women will consent to participate in the surveys (based on previous work by the research team [63]). Assuming 48 working weeks a year, and an intra-class correlation of 0.01, a sample of 200 women per month (approximately 67 women per each of the three time points: booking in visit, 27–28 weeks gestation, 35–36 weeks gestation) will give the study 80% power to detect an absolute increase in care provision of 15% in the intervention period (based on a conservative 50% estimate of prevalence of care provision at baseline) in at least one of the four primary outcomes at a 1.25% significance threshold. Assuming there are approximately 190 women eligible per week, a weekly sample of 72 women (i.e. 24 women per time point) with a 70% survey completion rate (*n* = 50) will result in the required number of women needed per month.

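### The only threshold given for the four primary outcomes is 1.25%; Holm's step-down test would keep the same 5% family-wise error and could show more outcomes

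*Protocol article*

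**What the plan says.** Under Primary trial outcomes the article states: "There are four primary outcomes for this trial". They are assessment with the AUDIT-C (1), brief advice (2), the advice and referral appropriate to the woman's risk (3), and outcomes 1 and 3 together (4). The wording of the fourth joins the two parts: "using the AUDIT-C and receiving, relative to their level of risk". Outcome 3 includes an advice element, which is also what outcome 2 measures.

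Under Sample size and power calculations, the article says that 200 women per month "will give the study 80% power to detect an absolute increase in care provision of 15% in the intervention period". The starting rate of care is taken to be 50%. Success for this calculation means a significant result "in at least one of the four primary outcomes at a 1.25% significance threshold".

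The Statistical analysis section describes a logistic mixed model for the primary outcomes. It gives no significance level and no multiplicity procedure. An overall 5% and the name of an adjustment method appear nowhere; both are inferred from 1.25% being 5% divided by four.

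**The concern.** A reader looking for the decision rule finds one number, 1.25%, and would naturally apply it to each outcome separately. Suppose three outcomes have p below 0.001 and the fourth has p = 0.03. The flat rule calls the fourth negative. Holm compares the largest of the four p-values with 5% once the other three are rejected, and calls it positive. Both rules hold the family-wise error at 5%, so the lost finding buys no extra error control. Each outcome reports on a particular element or combination of care, so it matters which of them succeed as well as whether any does.

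**Working it through.** **Inputs from the article:** four primary outcomes; 1.25% threshold; 80% power for at least one outcome; 72 women sampled per week; 70% completion; 48 working weeks a year. **Assumed, because not stated:** two-sided tests; equal effects on the four outcomes; one common correlation between the test statistics, varied from 0 to 0.9.

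**1. The plan's figures.** 0.05/4 = 0.0125, which matches exactly (the Šidák level would be 1 − 0.95^(1/4) = 1.274%). Monthly sample: 72 × 0.70 × 48/12 = 201.6, against 200 stated. The 80% power cannot be uniquely reproduced because the power model is not given, so two readings of it are carried through below.

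**2. Error control.** Holm orders the p-values and compares them with 0.05/4, 0.05/3, 0.05/2 and 0.05, that is 1.25%, 1.67%, 2.5% and 5%, stopping at the first failure. When no outcome has an effect, any false rejection requires the smallest p-value to be at or below 1.25%, so the error then equals that of the flat rule. Simulated, it is 4.9% at correlation 0, 4.3% at 0.5 and 3.2% at 0.8. When some effects are real, Holm still keeps the family-wise error at or below 5% under any dependence.

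**3. Power at each Holm step.** For a test with 80% power at 1.25%, the noncentrality is 2.498 + 0.842 = 3.339 (unrounded sum). Power at a later level is Φ(3.339 − critical value):

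| Level | Critical value | Power |
|---|---|---|
| 1.25% | 2.498 | 80% |
| 1.67% | 2.394 | 83% |
| 2.5% | 2.241 | 86% |
| 5% | 1.960 | 92% |

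**4. Flat rule against Holm.** Four equicorrelated normal statistics, 400,000 replicates per setting.

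*Reading A, the article's wording: 80% power for at least one outcome.* Per-outcome power at 1.25% was set so that this holds. At correlation 0 it is 1 − 0.20^(1/4) = 33%.

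| Correlation | Average power, flat → Holm | All four, flat → Holm |
|---|---|---|
| 0 | 33% → 38% | 1% → 7% |
| 0.5 | 50% → 58% | 20% → 38% |
| 0.8 | 63% → 71% | 45% → 63% |
| 0.9 | 69% → 75% | 57% → 72% |

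*Reading B: 80% power for each outcome at 1.25%.*

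| Correlation | Average power, flat → Holm | All four, flat → Holm | Holm shows at least one more |
|---|---|---|---|
| 0 | 80% → 89% | 41% → 69% | 33% of trials |
| 0.5 | 80% → 87% | 56% → 76% | 25% |
| 0.8 | 80% → 86% | 66% → 81% | 18% |
| 0.9 | 80% → 85% | 70% → 83% | 14% |

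As a check on reading B at correlation 0, the flat rule gives 0.80^4 = 41% for all four.

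**5. The plan's own criterion.** Power for at least one outcome is identical under the two rules in every setting (under reading B at correlation 0.5, for example, 96.7% and 96.7%), because Holm's first step is also 1.25%.

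**The case against.** The strongest reply is that nothing in the article is wrong. The 1.25% stands in a sample-size sentence. A reader might infer that the plan fixes a flat test at 1.25% for each outcome whatever the others show. The text does not say that: the Statistical analysis section commits to no procedure, and an analysis plan that is not shown may already specify a step-down test. This stands, and it limits the point to how the stated threshold should be used.

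Nor does the sample-size sentence need correcting. Its criterion is at least one significant outcome, and there Holm gains exactly nothing. This also stands.

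A reader might also infer that the overlap between outcomes makes 1.25% invalid, or is itself the reason for Holm. Neither follows. The flat rule is valid under any dependence, and overlap only makes it more conservative. Holm does not use the correlation either, and under reading B its gain shrinks as correlation rises (for all four outcomes, from 28 points at 0 to 13 at 0.9). What favours Holm is several effects being real at once.

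The larger gains assume 80% power for each outcome, which the article does not state, and showing all four is not a declared success criterion. Reading A is therefore the one closest to the text.

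Finally, a flat 1.25% has directly matching simultaneous 98.75% intervals, and Holm has no equally simple counterpart. That is a real but small cost.

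**Conclusion.** The point holds as an optional efficiency improvement, not as an error or contradiction. If 1.25% is applied flat, it gives up power on the later outcomes without gaining error control. On the article's definition of power, the average gain per outcome is about 5 to 9 percentage points, and the gain for all four is about 5 to 19 points, over correlations of 0 to 0.9. The sizes depend on equal effects, a common correlation and two-sided testing, none of which the article states. Two facts do not depend on these assumptions: Holm never rejects fewer outcomes than the flat rule, and both control the family-wise error at 5%. The 80% power for at least one outcome and the sample size are unaffected.

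**What to change.** In the Statistical analysis section, or in the analysis plan if one exists, state that the four primary outcomes are tested by Holm's procedure at a family-wise 5%, with ordered p-values compared with 1.25%, 1.67%, 2.5% and 5%. Keep 1.25% in the sample-size text and describe it as the first-step level. Settle this before outcome data are analysed, because a later switch would look data-driven. Individual 98.75% intervals can still be reported, with a note that they may not agree with a Holm rejection made at a later step. The cost is one or two sentences, with no extra data and no change in recruitment.
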